### Quality assurance and data management

Multiple measures will be taken to optimize the implementation of the research activities and ensure the quality of collected data. Before the study initiation, an investigator meeting will be organized, including the principal investigator, orthopedists and senior nurses from the participating orthopedic wards, statisticians, and research assistants. During the meeting, investigators will receive training about study design, implementation plan, and data collection and analysis for all intervention measures. In each orthopedic ward, an experienced staff (A) will be selected and trained about the key aspects of implementation details and further be responsible for monitoring and evaluation. Moreover, all the orthopedic wards will have a learning period within the first 10 days of interventions. Additionally, the measurements used in the study, such as the Caprini score, trauma index score, and VTE assessment, will be recorded [18]. EpiData 4.2 will be used to collect the trial data. In each ward, a trained staff (B) will collect data from HIS using standard CRF. Data cleansing will be conducted by another trained staff (C) every week to ensure the data check and management.

The SPIRIT reporting guidelines were used to ensure the completion of the study protocol (Additional file 1) [19].

### Data analysis

#### Statistical analysis principles

We will generally perform the analysis using the intention-to-treat (ITT) at the subject level for each outcome. All the participants with a recorded outcome will be included in the analysis according to the intervention group to which they have been randomized. Additionally, we will take the cluster-randomized crossover design effect into consideration. Adjustment for multiple comparisons among interventions will be used. The SAS 9.4 software will be used for all statistical analyses.

#### Handling of missing data

The least data missing will be expected. All-important observations will be collected and assessed by trained investigators. At the cluster level, orthopedic wards with incomplete patient recruitment will be included in the primary analysis of study outcomes, considering all participants available in each cluster. To assess the risk of bias related to orthopedic wards that have not completed patient recruitment, multiple imputations will be performed for the primary outcome and presented as sensitivity analyses. At the subject level, when a variable is missing, we will assume that most likely the missing variable has a normal or mean value.

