### Proposed sample size

We determined the sample size based on the cumulative incidence of VTE. It is estimated that at least 398 orthopedic trauma patients need to be enrolled in each of the five clusters to achieve a power value of 85% to detect an absolute difference of 10% in the cumulative incidence of VTE between the patients with intervention measures and those with control measures (assuming a VTE incidence of 15% according to our retrospective cohort study [5]) at a two-sided alpha level of 0.05. Consequently, approximately 40 patients will be enrolled per intervention measure/control measure per calendar month in each cluster, totaling 1990 patients. The intraclass correlation coefficient (ICC) was calculated based on two levels, 0.228 for patients within the same cluster/time period and 0.15 for patients within the same cluster/different time periods. Due to the lack of data on ICCs related to the current study design and primary outcome, we chose to use a conservative ICC value in our sample size estimation. Moreover, considering a 20% loss of participants, we determine to enroll a total of 2490 patients in the trial, with 498 in each cluster.

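### The single-value rule for missing patient data does not exclude VTE, and the only multiple imputation stated is aimed at under-recruited wards rather than at enrolled patients without a result

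*Protocol article*

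**What the plan says.** The protocol article treats missing data at two levels in its section on handling of missing data.

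- **Ward level.** Wards that fall short of their recruitment stay in the primary analysis, "considering all participants available in each cluster". A sensitivity analysis is added: "To assess the risk of bias related to orthopedic wards that have not completed patient recruitment, multiple imputations will be performed for the primary outcome".
- **Patient level.** The rule is that "when a variable is missing, we will assume that most likely the missing variable has a normal or mean value". No variable is exempted and no sensitivity analysis is attached.

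The section on statistical analysis principles defines the analysis set: "All the participants with a recorded outcome will be included in the analysis according to the intervention group to which they have been randomized".

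On the amount of missing data, the missing-data section expects very little, while the sample size section inflates enrolment "considering a 20% loss of participants", to 2490 in total and 498 per cluster. VTE is ascertained by ultrasound (data collection section), and the primary effect measure is a risk ratio with a 95% CI from GEE (primary analysis section).

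**The concern.** The patient-level rule speaks of any variable, so on its wording it reaches VTE and 30-day death. A patient who was not scanned has unknown VTE status. Setting that status to normal would count a missing scan as a success. Setting it to the mean would give a fractional outcome that adds apparent sample size without information. Under the analysis-set rule the same patient would be left out. The document does not say which rule prevails for outcomes, so the choice could be made after the data have been seen.

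Multiple imputation, the one principled method named, is attached to a different problem. A ward that under-recruits lacks people who were never enrolled, and they bring no data. For enrolled patients with a missing VTE result, the document states no sensitivity analysis.

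Loss could plausibly differ between measures in this design. All patients in a ward in a given month receive the same measure. The caption of Fig. 1 shows ten monthly periods per cluster, which is about two per measure per ward if the five measures share them evenly. A month with poor scanning or follow-up therefore falls wholly on one measure.

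**Working it through.** **Inputs from the document.** Assumed VTE incidence 15%; absolute difference 10 points (taken here as 15% v 5%); two-sided alpha 0.05; 398 patients per cluster and 1990 in total before loss; 20% loss; 498 per cluster and 2490 in total after inflation. **Assumptions made here.** Loss by measure, which the document does not give; 498 patients per measure (2490 / 5); independent patients.

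**1. The plan's own figure.** 398 / (1 − 0.20) = 497.5, rounded up to 498; 5 × 498 = 2490. This reproduces. A 20% loss from 2490 is 0.20 × 2490 = 498, or about 500 patients.

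**2. Missing VTE coded as normal (no VTE), equal loss.** Observed risk = p × (1 − d).
- 0.15 × 0.80 = 0.12 and 0.05 × 0.80 = 0.04.
- Risk difference: 0.12 − 0.04 = 0.08, against a true 0.10.
- Risk ratio: 0.04 / 0.12 = 0.333, unchanged from 0.05 / 0.15.

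**3. The same coding, unequal loss, no true effect (15% in both).**

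| Loss, control / intervention (assumed) | Observed risks | Risk ratio |
|---|---|---|
| 15% / 25% | 0.1275 / 0.1125 | 0.88 |
| 10% / 30% | 0.135 / 0.105 | 0.78 |
| 25% / 15% | 0.1125 / 0.1275 | 1.13 |

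The error favours whichever measure loses more patients. With 498 per measure and clustering ignored, the chance of a significant result in favour of the intervention is about 11% in the first row and 31% in the second. A valid two-sided 5% test would allow 2.5% in that direction.

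**4. Missing VTE filled with the mean of the measure.** With n observed and N after filling, the variance shrinks by n/N while the apparent sample size rises to N. The ratio of the naive to the complete-case standard error is √[(n/N)/N] / √(1/n) = n/N = 398/498 = 0.80. A nominal 5% test then has size 2 × [1 − Φ(1.96 × 0.80)], about 11.7%. This is a patient-level figure.

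**5. Multiple imputation for an under-recruited ward.** In a simulation, 300 patients were observed against a target of 398 at a risk of 15%, and the shortfall was imputed from the observed patients.
- Mean estimate: 0.1502 with imputation, 0.1499 without.
- Standard error: 0.0206 with, 0.0205 without.
- Correlation between the two estimates: 0.999.

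The imputation returns the available-case result.

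**The case against.** A reader might infer that the plan will code lost patients as free of VTE. The documents do not establish that. The analysis-set rule requires a recorded outcome, and under it such patients are left out. Normal or mean values suit scored items such as the Caprini and trauma index scores better than a binary endpoint. The two sections can be read as consistent: outcomes need a record, and covariates receive a default. This objection stands in part. What is shown is an unresolved scope, not a settled plan to count losses as successes. But the covariate-only reading has to be supplied by the reader, because the text does not state it.

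A reader might also infer that the misplaced imputation harms the main result or creates false precision. It does not. It is a sensitivity analysis, the primary analysis already uses all available participants, and the simulation shows no gain in precision. The article also does not say outright that records will be created for people never enrolled. Borrowing from other wards or months could shift weights somewhat. None of this supplies an analysis for enrolled patients with missing VTE.

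The sizes are conditional as well. Equal loss leaves the primary risk ratio intact. The unequal losses are assumptions. The 20% is a sample-size allowance for loss of participants, not a forecast of missing scans. The 20% shortfall in the standard error need not carry over to a GEE that accounts for clustering: if the ward-month mean were filled in, ward-month means would not move, and the text does not say which mean is meant.

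Imputation predictors and tipping-point details commonly belong in an SAP that is not shown. The point here is that a stated rule is loosely scoped and a stated method is aimed at the wrong patients, not that such detail is absent.

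**Conclusion.** The concern holds as a should-fix. The two sections give an enrolled patient without a VTE result two possible treatments and must be reconciled.

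If the single-value rule were applied to VTE, coding as normal would lower the absolute risks and cut a 10-point difference to 8 at an equal 20% loss, with no change in the risk ratio. The primary risk ratio is distorted only if loss differs between measures: to about 0.88 or 0.78 under the assumed 15% v 25% or 10% v 30%, and in the other direction if the imbalance is reversed. Mean filling would overstate patient-level precision by the factor shown above, clustering ignored.

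If the rule was meant for covariates only, these distortions of the outcome do not arise. The stated multiple imputation would still leave enrolled patients with missing VTE unaddressed.

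**What to change.** - State that outcomes (VTE, operative bleeding, 30-day death) are never filled with a normal or mean value.
- Keep enrolled participants with a recorded outcome as the primary analysis set, as the analysis principles already say. An under-recruited ward-month simply has a smaller n, and nobody who was not enrolled is imputed.
- Redirect the sensitivity multiple imputation to enrolled patients with missing VTE, using measure, ward, month and the recorded baseline variables (Caprini score, TI score).
- Add a best/worst-case or tipping-point table by measure, so that readers can see how far unequal loss would have to go to change the conclusion.

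The cost is a change of analysis wording and a little extra programming. The variables named are already recorded, so no new data are needed. The wording should be settled before outcomes are analysed.

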### Subject flow

Figure 2 displays the flow of the trial.

**Fig. 2 Fig2:**
[figure not shown]
Study flow diagram. *ITT*, intention-to-treat

### Primary analysis

For the primary outcome of the study, the incidence of VTE will be presented as risk ratio and 95% CIs. Generalized estimating equation (GEE) will be deployed to compare differences and adjust cluster effect, period effect, and interaction among interventions and periods if applicable.

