## Methods and analysis

### Study design

This study is a cluster-randomized crossover, multicenter exploratory trial that is designed to assess the safety and efficacy of multiple intervention measures for preventing VTE among perioperative orthopedic trauma patients. The unit of randomization is the orthopedic wards, and each ward will define a cluster, as the proposed interventions are designed to be implemented in all orthopedic wards rather than in selected individual subjects. The study will be conducted at four hospitals in Shanghai from December 2019 through December 2023, including (1) Shanghai Sixth People’s Hospital, Shanghai Jiao Tong University School of Medicine; (2) Jinshan Branch of Shanghai Sixth People’s Hospital, Shanghai Jiao Tong University School of Medicine; (3) Lingang Compound of Shanghai Sixth People’s Hospital, Shanghai Jiao Tong University School of Medicine; and (4) Shanghai Tenth People’s Hospital, Tongji University. A total of five clusters will be determined in the study, according to the routine amount of orthopedic trauma patients visited in those hospitals.

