### Interventions

A total of four intervention measures and one control measure will be implemented as follows.

Intervention 1: Fraxiparine (Glaxo Smith Kline, England) nadroparin calcium will be given once a day subcutaneously, with the dosage of 100 Axa IU/kg taking patient’s body weight into account.

Intervention 2: Clexane (Sanofi, France) enoxaparin sodium will be given once a day subcutaneously, with the dosage of 100 Axa IU/kg taking patient’s body weight into account.

Intervention 3: Fraxiparine (Glaxo Smith Kline, England) nadroparin calcium will be given once a day subcutaneously, with the dosage of 100 Axa IU/kg taking patient’s body weight into account. In addition, IPC (Wonjin Mulsan, China) will be administered twice a day, 20 min each time.

Intervention 4: Clexane (Sanofi, France) enoxaparin sodium will be given once a day subcutaneously, with the dosage of 100 Axa IU/kg taking patient’s body weight into account. In addition, IPC (Wonjin Mulsan, China) will be administered twice a day, 20 min each time.

Control: There is no predetermined intervention. The prophylaxis measure against VTE will be administered based on the orthopedists’ decision for the best of patients. The details of the measures will be recorded.

These intervention measures and control measure will alternate along with calendar months (Fig. 1), which means orthopedic trauma patients enrolled in the study will be administered with same measures per cluster per calendar month.

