### Randomization and allocation

In this study, five clusters will equally share the proposed sample size. In the implementation, each cluster receives several sequences of intervention periods (including four diverse intervention measures) and control periods, which is determined by a randomization, to achieve the allocated sample size (Fig. 1).

Additionally, orthopedic trauma patients are randomly included in these clusters, which might result in a slightly different number of enrolled participants over the periods across the clusters. Thus, we define the duration of a calendar month for each intervention or control period in these clusters, which may ensure the clusters achieve the sample size within the identical number of sequences.

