### Subgroup analysis

For the primary outcome, efficacy among interventions will be determined according to the Caprini score and TI score, as well as sociodemographic and clinical groups. To test for interactions, the consistency of intervention effect across the subgroups will be assessed. Bonferroni correction will be used to adjust subgroup analyses for multiple comparisons.

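### The stated primary model has no patient-level covariate, although the Caprini and trauma index scores are recorded and only about 10 to 12 ward-months form each arm; adding both scores would remove some avoidable chance error

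*Protocol article*

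**What the plan says.** All references are to the protocol article.

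- **Primary analysis:** "the incidence of VTE will be presented as risk ratio and 95% CIs", and the GEE is to "adjust cluster effect, period effect, and interaction among interventions and periods if applicable". The abstract names the same terms, and Secondary analysis applies them to all its analyses. None of these places names a patient-level covariate.
- **Quality assurance and data management:** measurements "such as the Caprini score, trauma index score, and VTE assessment, will be recorded".
- **Inclusion criteria:** a Caprini score above 2 is required, so this score must be known at enrolment.
- **Subgroup analysis:** "efficacy among interventions will be determined according to the Caprini score and TI score, as well as sociodemographic and clinical groups". This is the only analytic use stated for either score.
- **Study design and Interventions:** the ward is the unit of randomisation, and all patients enrolled in a ward in one calendar month get the same measure. "A total of five clusters will be determined in the study", and there are five measures (four interventions and one control).
- **Randomization and allocation:** "orthopedic trauma patients are randomly included in these clusters".

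**The concern.** What is randomised is the order of measures across months within a ward. Patients arrive with their injuries and are enrolled under whatever measure is in force. The statement that they enter clusters at random does not describe this design, and it suggests a protection against case-mix differences that the design does not give.

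Because every ward is to receive all five measures, stable differences between wards are balanced by design, and ward and period are in the model. Neither handles a month in which one ward happens to admit higher-risk patients. With few ward-months per measure, such differences need not average out.

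There is a second route. Nothing in the article says that the month's measure is concealed from those who enrol, or that enrolment is consecutive. Some eligibility items call for judgement, such as stable vital signs, contraindications and high bleeding risk. If these were applied differently under different measures, the arms would differ systematically. Recorded risk scores in the model would give partial protection; ward and period terms would give none.

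**Working it through.** **1. Ward-months per measure.** The inputs are 1990 patients, or 2490 with the allowance for loss, and about 40 per ward-month (Proposed sample size); 5 measures (Interventions); 5 wards (Study design); and 10 periods per ward (Fig. 1 caption, which calls them hypothetical).

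- 1990 / 40 / 5 = 9.95, which agrees with 5 wards × 10 periods / 5 measures = 10.
- 2490 / 40 / 5 = 12.45.
- If monthly intake is below 40 the count rises. The window from December 2019 to December 2023 has 49 calendar months, so the ceiling is 49 × 5 / 5 = 49.

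**2. Month-to-month variation implied by the plan.** The stated ICCs are 0.228 within a ward-month and 0.15 between months of one ward. The month component is 0.228 − 0.15 = 0.078, and the patient component of a ward-month mean is (1 − 0.228) / 40 = 0.0193. The month share, leaving out the stable ward component, is 0.078 / (0.078 + 0.0193) = 80%. How much of this is case mix is not stated.

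**3. Chance imbalance in a score (assumed inputs).** Take 400 patients per measure in ward-months of 40, and let ρ be the ward-month ICC of the score.

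- SD of the difference in mean score between two measures, in score SDs: √[2 × (1 + 39ρ) / 400].
- 95% range of the resulting shift in the risk ratio: exp[± 1.96 × SD × ln(OR) × (1 − 0.10)]. Here 0.10 is the midpoint of 15% and 5%, reading the planned 10-point difference as a reduction from 15%.

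**4. Gain from adjustment (simulation).** The simulation has 5 wards, 10 months and 40 patients per ward-month, with each measure twice per ward in random order. There is no treatment effect, and incidence is about 15%. A linear model with measure, ward and period is fitted with and without the score, in 1000 runs per scenario.

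| Score ICC ρ | OR per SD | SD of difference | 95% range of risk-ratio shift | Variance with score / without |
|---|---|---|---|---|
| 0 | 1.5 | 0.071 | 0.95 to 1.05 | 0.97 |
| 0 | 2 | 0.071 | 0.92 to 1.09 | 0.94 |
| 0.05 | 1.5 | 0.121 | 0.92 to 1.09 | 0.96 |
| 0.05 | 2 | 0.121 | 0.86 to 1.16 | 0.83 |
| 0.10 | 1.5 | 0.157 | 0.89 to 1.12 | 0.94 |
| 0.10 | 2 | 0.157 | 0.83 to 1.21 | 0.79 |

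The variance falls by about 3% to 21%. The mean error in the risk difference is about zero in every scenario, with or without the score (at most 0.003).

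**5. Limit of step 4.** In that simulation the score is the only thing that varies from month to month within a ward. If the month component is as large as the plan's 0.078 and mostly unrelated to the score, the relative gain is smaller. As a linear approximation, the share removed is (ln OR)² × p(1 − p) × (1 + 39ρ) / (1 + 39 × 0.078), with p(1 − p) = 0.15 × 0.85 = 0.1275 and a denominator of 4.042.

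- Mild end (OR 1.5, ρ = 0): 0.1644 × 0.1275 × 1 / 4.042 = 0.5%.
- Strong end (OR 2, ρ = 0.10): 0.4805 × 0.1275 × 4.9 / 4.042 = 7.4%.

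**The case against.** The strongest objection is that a covariate list is commonly left to the statistical analysis plan, which is not shown, and that an analysis without covariates is valid in a randomised trial. Both parts are right as far as they go. A reader might infer that the final analysis will certainly be unadjusted; the article does not show that, because it never says that no other variable will enter. The point stands on narrower ground: the article does state an adjustment set, repeats it, and gives the two scores a different role. A better method using data already collected can be recommended against that stated set.

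A reader might also infer that the risk ratio will be biased. The documents do not support this. With a random sequence in every ward, leftover case-mix differences are chance error, and the simulated mean error is about zero. Bias needs selective enrolment, which no section describes. If it occurred, adjustment would correct only the part that the scores capture.

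Three further limits stand:

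- The model is not confined to ward and period, since the interaction term is named too.
- The article gives no prognostic strength for either score, and requiring a Caprini score above 2 narrows its range. To call them strong predictors goes beyond the text.
- The 80% month share is not the amount that adjustment would remove. It rests on ICCs that the article says were chosen conservatively for lack of data, and case mix is an unknown part of it.

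**Conclusion.** The point holds as a recommendation on precision and prespecification. It does not show that the primary analysis is invalid. The stated GEE terms include no patient-level covariate while two recorded risk scores are kept for subgroups, and the number of randomised units per measure is small: about 10 to 12 if 40 patients are enrolled per ward-month.

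The benefit is small to moderate and cannot be fixed from the documents. Adjustment lowers contrast variance by about 3% to 21% if the score has an odds ratio of 1.5 to 2 per SD, a ward-month ICC of 0 to 0.10, and is the only source of month-to-month variation. It lowers it by roughly 0.5% to 7% if months also vary as much as the plan's ICCs imply, for other reasons. Partial protection against differential enrolment comes on top and cannot be quantified.

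The sentence on random inclusion of patients needs correcting whatever the analysis plan contains, because it conflicts with the Study design and Interventions sections.

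**What to change.** 1. In Primary analysis, add the baseline Caprini score and baseline TI score, both continuous, to the named GEE terms. Use values recorded before the month's measure could affect them. Fix this before outcomes are compared by measure.
2. Keep the marginal risk ratio as the reported effect, by standardising predicted risks over all analysed patients.
3. Report the result without the two scores, with the same ward, period and interaction terms, as a sensitivity analysis.
4. In Randomization and allocation, replace the statement that patients are included at random with one saying that all eligible patients admitted in the ward-month are enrolled. If that was not the practice, say how patients were selected.

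The cost is wording plus one extra analysis step, the standardisation. No new data item is needed, since both scores are already recorded. The Caprini score is required for eligibility and so should be complete; the completeness of the TI score should be checked before it is relied on.
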